#### Cost-effectiveness analyses

The effects and costs of Featback and/or online support from an expert patient will be compared to those of usual care (i.e., participants in the waiting list condition) from a societal perspective, including healthcare costs and non-healthcare costs. No discounting will be applied due to the time horizon of the economic evaluation of 1 year.

The effects of an intervention will be assessed with the EQ-5D-5 L at baseline and subsequent follow-up measurements. The EQ-5D-5 L results will be translated into utilities using the EQ-5D-5 L with Dutch rates [92]. The quality-adjusted life year (QALY) outcome per patient will be obtained by using the area-under-the-curve method for the utility scores obtained for each patient.

Outcomes of patients in terms of capabilities instead of QALYs will also be calculated using the ICECAP-A by means of the UK general population tariff (no Dutch tariff is available) [93], since results from this instrument might reflect outcomes of psychiatric patients better than the EQ-5D-5 L results [71].

The costs will be divided into healthcare costs and non-healthcare costs. Healthcare costs are calculated by summing the costs of Featback and/or online support from an expert patient, and other healthcare use during the first year of follow-up. Intervention costs of Featback include the maintenance of the program and website and payment to a psychologist following the procedure when a user develops severe ED pathology while using Featback. Intervention costs of expert-patient support are estimated by multiplying the time spent on sessions by their hourly pay rate. Costs for supervision of expert patients are also included, by multiplying the time spent at supervision by their hourly pay. Healthcare use is assessed with the TiC-P Midi [74], which records the number of contacts with care providers and use of medication during the last months (i.e., the period between every follow-up measurement). The costs will be calculated by multiplying the number of contacts with a specific healthcare provider by the reference unit price of the corresponding healthcare service [75, 76]. Additionally, non-healthcare costs, including costs related to productivity losses at work through being absent or being less productive and having difficulties in performing unpaid work such as domestic tasks, are estimated. Costs related to absenteeism will be calculated according to the friction cost method, which means that the absent hours are multiplied by the average gross hourly wage per paid working individual in the Netherlands with a maximum of 12 weeks, the friction period in the Netherlands [75, 76]. The friction period is the timespan organizations need to restore the initial production level [94]. Costs related to reduced efficiency at work are calculated based on the amount of hours of work participants estimate they need in order to catch up for all the work they were unable to perform because of health problems. These hours are again multiplied by the average gross hourly wage per paid working individual in the Netherlands, based on age and gender. Costs related to difficulties in performing unpaid work are calculated by multiplying the amount of hours that others would need to take over the unpaid work of the participant by the average gross hourly wage of a domestic worker. In summary, total costs of an intervention can be estimated by summing the healthcare costs (including the intervention costs) and non-healthcare costs consisting of productivity costs (including absenteeism, reduced efficiency at work, and difficulties performing unpaid work).

Differences in mean costs and effects per patient between interventions will be compared using a two-sided *t* test. The uncertainty regarding mean costs and effects per participant will be estimated using bootstrapping in Microsoft Excel, simulating 1000 bootstrap samples. Specifically, 1000 samples will be drawn from the original sample to estimate the sampling distribution and its 95% confidence interval. The results of the bootstrapping will be represented in cost-utility acceptability curves. These curves illustrate the probability that an intervention (i.e., Featback) is cost-effective in comparison with the alternative (i.e., care as usual) for a range of ceiling ratios, which are the maximum amount of costs a society is willing to pay for one unit change in outcome (i.e., QALY).

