#### Waiting list control

Participants will be placed on a waiting list for 14 months (matching the participation duration of participants in the other conditions; 8-week intervention period plus 1 year follow-up), after which they will be offered 8 weeks of Featback with support from an expert patient. Participants in this condition will be asked to complete the same assessements as participants in the other conditions (i.e., T0-T5). Note that participants in all conditions are allowed to seek and receive treatment and take medication.

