##### Direct medical costs

The Trimbos/iMTA questionnaire for Costs associated with Psychiatric Illness (TiC-P, Midi version [74]) will be used to calculate the total direct medical costs. The TiC-P assesses medical treatment utilization (e.g., number of contacts with the general practitioner, medical specialists, and paramedics) and medication use during the last 3 months. Additionally, the Midi version of the questionnaire is significantly shorter, reducing the burden for participants, while retaining 90% of the total cost estimated by the full version [74]. The direct medical costs will be calculated using the Dutch guidelines for cost calculations in healthcare [75]. Reference unit prices of the corresponding health care services will be applied [75, 76].

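### The cost-utility plan forgoes baseline adjustment, names no incremental analysis for the cost-effectiveness part of H2, and states a 1-year horizon that does not match T0 to T5

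*Protocol article*

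**What the plan says.** All references are to the protocol article.

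- **Comparison of arms** (Cost-effectiveness analyses): "Differences in mean costs and effects per patient between interventions will be compared using a two-sided" *t* test. Uncertainty is handled separately: "The uncertainty regarding mean costs and effects per participant will be estimated using bootstrapping in Microsoft Excel, simulating 1000 bootstrap samples". The bootstrap output feeds the acceptability curves. No baseline covariate is named for costs or effects.
- **Effects** (same section): these "will be assessed with the EQ-5D-5 L at baseline and subsequent follow-up measurements", and QALYs are the area under each patient's utility curve.
- **Comparator** (same section): effects and costs of Featback and/or support "will be compared to those of usual care", identified with the waiting list. The acceptability curves are likewise set against care as usual.
- **Hypothesis** (Aims and research questions): H2 includes the claim that Featback plus expert-patient support is more cost-effective than either one alone.
- **Horizon** (Cost-effectiveness analyses): discounting is omitted "due to the time horizon of the economic evaluation of 1 year". Healthcare costs sum the intervention costs "and other healthcare use during the first year of follow-up".
- **Visit schedule**: the Design section counts T2 to T5 from T1, which falls after the 8-week period. The Waiting list control section gives the whole duration as 14 months, that is, "8-week intervention period plus 1 year follow-up".
- **Cost recall** (Direct medical costs): the TiC-P covers care and "medication use during the last 3 months".

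**The concern.** Cost-effectiveness belongs to the first aim and to both main hypotheses, so the economic analysis carries real weight. Three features weaken it.

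1. An area-under-the-curve QALY contains the T0 utility and is correlated with it at every later visit. A plain difference in means leaves that predictable variation in the error term, although the covariate is already collected.
2. H2 makes a claim about combination versus component. The clinical half of H2 gets post hoc comparisons across the four conditions (Intervention effectiveness analyses). The economic half gets no matching contrast.
3. The horizon governs which costs and which QALYs enter the ratio. If its start and end are left open, the window can be chosen once results are known, and costs and effects might be cut at different points.

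**Working it through.** **Plan's own figure.** The article gives no precision or sample-size figure for the cost-utility analysis. Its total of 264 concerns the clinical outcome. It reproduces: λ = 0.15² × 264 × 2 / (1 + 0.5) = 7.92, which gives power 0.801 at α = 0.05 with two groups. It does not bear on this point.

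**1. Precision lost without T0 utility**

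Inputs from the article: visits at T0, at 8 weeks, and 3, 6, 9 and 12 months after T1. Taking 3 months as 13 weeks, these fall at weeks 0, 8, 21, 34, 47 and 60. Assumed: utilities have equal variance at all visits and one common correlation ρ between any two. The article's only stated correlation, 0.5, is for the primary outcome from T0 to T1.

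Trapezium weights in years are 0.077, 0.202, 0.25, 0.25, 0.25 and 0.125. Their sum is W = 1.154 and their sum of squares is 0.250.

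- Slope of QALY on T0 utility: b = 0.077 + ρ(1.154 − 0.077)
- QALY variance, in units of the utility variance: v = (1 − ρ) × 0.250 + ρ × 1.154²
- Share explained: R² = b²/v
- Ratio of adjusted to unadjusted standard error: √(1 − R²)

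| ρ (assumed) | b | v | R² | SE ratio | Unadjusted SE relative to adjusted |
|---|---|---|---|---|---|
| 0.3 | 0.40 | 0.574 | 0.28 | 0.85 | 1.18 |
| 0.5 | 0.62 | 0.791 | 0.48 | 0.72 | 1.39 |
| 0.7 | 0.83 | 1.007 | 0.69 | 0.56 | 1.78 |

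Scale: with an assumed utility SD of 0.20 and 88 per arm, the standard error of a chance T0 difference is 0.20 × √(2/88) = 0.030. Multiplied by b, a one-standard-error imbalance moves the unadjusted QALY difference by 0.012, 0.019 or 0.025 at the three correlations.

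**2. Comparator against hypothesis**

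No arithmetic applies. H2 needs combination versus Featback and combination versus support. The section's opening sentence compares with the waiting list, and the curves compare with care as usual. The one phrase that could reach active arms is the *t* test between interventions. That test treats costs and effects separately, so it gives neither an incremental ratio nor a probability of cost-effectiveness for those two contrasts.

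**3. Horizon**

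T0 to T5 is 8 + 52 = 60 weeks, which is 8/52 = 15% longer than one year (14/12 gives 17%). The stated year can be placed in three ways:

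- *From T0*: it ends at week 52, between T4 (week 47) and T5 (week 60), where there is no visit.
- *From T1*: the baseline utility and the 8-week period, when intervention costs arise, lie outside it.
- *T0 to T5*: it is not one year.

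At an assumed utility of 0.6 to 0.8, the extra 8 weeks carry 0.6 × 8/52 = 0.09 to 0.8 × 8/52 = 0.12 QALY per person. This is added in every arm, so most of it cancels in a difference between arms.

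If the TiC-P is given at T1, a 13-week recall reaches 13 − 8 = 5 weeks before T0.

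**The case against.** **Bias.** A reader might infer that the *t* test biases the QALY difference through baseline imbalance. It does not. Randomisation makes the unadjusted difference unbiased, and its standard error and bootstrap interval already allow for chance imbalance. The loss is of efficiency. Covariates are also often left to an analysis plan, but here the article does fix a method, and that method has no covariate. The gain depends on assumed correlations, hence the range down to 28%.

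**Mismatched windows.** It is tempting to say that a 60-week QALY will be divided into a 52-week cost. The article does not say so. It gives one horizon for the whole evaluation, never states that QALYs run to T5, and does not define where the first year of follow-up starts. What stands is that the stated year does not match T0 to T5 and has no start.

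**Contradictory recall.** A reader might also see a conflict between the TiC-P's 3-month recall and the later statement that it covers the time between follow-up measurements. The two agree for T2 to T5, which are 3 months apart. A problem arises only if a T1 TiC-P is used, and Table 2, which would show this, is not available in the text reviewed.

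**Only the waiting list.** The wording between interventions may include active pairs, and the first aim mentions them. All arms complete the same T0 to T5 assessments, so the trial can answer H2 once the contrasts are named. The gap is in the stated analysis and not in the data.

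**Conclusion.** The point stands as one that should be addressed, in three parts.

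- **H2 (the strongest part).** The plan as written gives no incremental cost-utility result for combination versus either component. This follows from the text and rests on no assumption.
- **Horizon.** One year does not describe T0 to T5, which is 8 weeks plus 12 months, and its start is undefined. That costs and QALYs will actually be cut at different points is an inference that the article does not establish.
- **Baseline adjustment.** Omitting it is valid but wasteful. The recoverable share of QALY variance is about 28% to 69%, for assumed correlations of 0.3 to 0.7 with equal variances. The shift of 0.012 to 0.025 QALY also needs the assumed SD of 0.20.

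**What to change.** 1. **Adjust.** Within each bootstrap sample, estimate the QALY difference by regression on arm and T0 utility. Do the same for costs on arm and T0 costs, if T0 costs are collected.
2. **Name the H2 contrasts.** Add incremental cost-utility results and acceptability curves for combination versus Featback and for combination versus expert-patient support, beside the comparisons with the waiting list. Two contrasts are enough for H2. A ranking of all four arms is optional.
3. **State one horizon.** Use T0 to T5 for all costs and all QALYs, correct the one-year wording, and restate the reason for not discounting to fit.
4. **Handle T1 recall at analysis.** If the TiC-P is given at T1, scale its 3-month recall to the 8 weeks since T0 (8/13 = 0.62). This assumes even use over the recall period, which should be stated. Do not reword the questionnaire: recruitment began on 8 October 2018, and a change mid-trial would mix recall periods between participants.

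The cost is a few sentences in the plan and a little more analysis. The regressions can be run in R, which the Statistical analyses section already names. No new participants, visits or questionnaires are needed.

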#### Intervention effectiveness analyses

To investigate the effectiveness of Featback with and without weekly expert-patient support, within-group and between-group effect sizes (Cohen’s *d*) will be calculated (i.e., the effects of time and intervention) using the pooled standard deviation of each group. We are mainly interested in the effect from baseline to post-intervention (T0–T1), but to see if effects are maintained over the short and long term, analyses will be repeated for T1–T3 and T1–T5 respectively.
 To answer the first and main hypothesis that the active interventions (i.e., Featback, expert-patient support, and Featback plus expert-patient support) are more effective than a waiting list in reducing ED symptomatology (i.e., primary outcome EDE-Q global score), the three active intervention conditions will be compared to the waiting list condition. Repeated measures ANOVA will be used for T0–T1 to test this hypothesis. To see if the effects are maintained, these analyses are repeated for T1–T3 and T1–T5. The second hypothesis was that the combination of Featback and expert-patient support would be more effective than Featback or expert-patient support alone. A repeated measures ANOVA with post hoc tests will be conducted to compare T0–T1 differences in ED symptomatology between the four conditions. The post hoc analyses apply the Bonferroni correction for multiple testing. To see if these effects are maintained, these analyses are repeated for T1–T3 and T1–T5.

These confirmatory analyses will be repeated controlling for significant baseline variables (i.e., age, duration of ED psychopathology, number of psychological healthcare appointments). Additionally, the main analyses will be repeated for completers only.

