Additionally, some limitations of the current study design should be noted. Firstly, participants are allowed to engage in treatment outside of the research for ethical reasons. Although we will control for healthcare appointments during the analyses, methodologically it would be preferable to have all the participants only receive the experimental intervention. Lastly, only online measures will be completed by participants. This limits the diagnostic accuracy, introduces recall bias, and might reduce intervention usage as well. Indeed, we expect a fairly high dropout rate, and missing data might not be at random, which will need to be taken into account when analyzing the data. Nevertheless, the current approach is needed to maintain the low threshold and anonymity of the intervention, making it possible to generalize beyond this study to the real effects of Featback with and without expert-patient support.

The (cost-)effectiveness of Internet-based interventions in combination with expert-patient support for the (early) interventions of individuals with an ED or related symptoms has not been investigated before. Results on this subject will contribute to the delivery of e-mental health and expert-patient support and help to guide individuals with eating problems to the care they need.

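### QALYs are compared by an unadjusted t test and bootstrap although baseline utility is collected, so precision is given away and chance baseline imbalance carries into the cost-effectiveness result

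*Protocol article*

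**What the plan says.** All of this is in the protocol article, under Cost-effectiveness analyses unless stated otherwise.

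- **Utility measurement.** "The effects of an intervention will be assessed with the EQ-5D-5 L at baseline and subsequent follow-up measurements".
- **QALY.** The "outcome per patient will be obtained by using the area-under-the-curve method for the utility scores obtained for each patient".
- **Comparison.** "Differences in mean costs and effects per patient between interventions will be compared using a two-sided" *t* test.
- **Uncertainty.** "1000 samples will be drawn from the original sample to estimate the sampling distribution and its 95% confidence interval"; the bootstrap results feed the acceptability curves.
- **Cost window.** Healthcare costs are the intervention costs plus "other healthcare use during the first year of follow-up".

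Covariates are mentioned in two other places. Under Intervention effectiveness analyses, "These confirmatory analyses will be repeated controlling for significant baseline variables" refers to the EDE-Q tests of the first two hypotheses and lists age, duration of eating-disorder psychopathology and number of psychological healthcare appointments. The Discussion adds "Although we will control for healthcare appointments during the analyses", without naming a model or an outcome. Neither place mentions baseline utility or baseline cost. The baseline homogeneity tests under Statistical analyses are not linked to the economic comparison.

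**The concern.** A person's utility at baseline predicts utility at later visits. If the area under the curve starts at T0, baseline utility is also a small part of the outcome itself. A *t* test on raw QALYs, and a bootstrap of raw means, leave this predictable variation in the error term. They also let whatever baseline difference chance produces between two arms pass into the estimated QALY difference.

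The first two hypotheses (Aims and research questions) both include cost-effectiveness, and the QALY difference is the effect side of every acceptability curve. If QALY effects are small, an avoidable loss of precision or a modest baseline imbalance can visibly move a curve. The baseline measurement that would remove most of this is already in the data.

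**Working it through.** **Inputs from the article.** Assessments are at T0, at T1 (8 weeks), and at 3, 6, 9 and 12 months after T1 (Design); I take weeks 0, 8, 21, 34, 47 and 60. The planned number is 88 per condition (Sample size calculation). The article gives no figure for the QALY comparison, so there is none to reproduce.

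**Inputs assumed, because the article gives none for utility.** The correlation of T0 utility with each follow-up utility is r = 0.3 to 0.6. The only related figure in the article is 0.5, stated for the primary outcome over T0–T1. The correlation between follow-ups is 0.7. Utility variance is equal at all visits, with SD 0.20 where an absolute size is needed.

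**Step 1: weights.** Trapezoid weights in years for T0 to T5 are 0.077, 0.202, 0.25, 0.25, 0.25 and 0.125, which sum to 1.154. The direct share of T0 is 0.077/1.154 = 6.7%. The follow-up weights sum to F = 1.077 and their squares sum to 0.244.

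**Step 2: slope of QALY on baseline utility.** b = w0 + r × F. At r = 0.5, b = 0.077 + 0.5 × 1.077 = 0.615. Of this, 0.077 is the direct weight and 0.538 comes through correlation with later utilities.

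**Step 3: QALY variance, in units of the utility variance.** V = w0² + 2·w0·r·F + (0.3 × 0.244 + 0.7 × F²). At r = 0.5, V = 0.006 + 0.083 + 0.885 = 0.974.

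**Step 4: gain from adjustment.** R² = b²/V = 0.615²/0.974 = 0.389. The ratio of adjusted to unadjusted standard error is √(1 − R²) = 0.782, a cut of 22%. That is worth a factor of 1/(1 − 0.389) = 1.64 in sample size.

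| Case (0.7 between follow-ups) | Slope b | R² | SE cut |
|---|---|---|---|
| T0–T5, r = 0.3 | 0.400 | 0.17 | 9% |
| T0–T5, r = 0.4 | 0.508 | 0.27 | 15% |
| T0–T5, r = 0.5 | 0.615 | 0.39 | 22% |
| T0–T5, r = 0.6 | 0.723 | 0.53 | 31% |
| T0–T5, r falling from 0.5 at T1 to 0.3 at T5 | 0.515 | 0.28 | 15% |
| T1–T5 only, r = 0.3 | 0.300 | 0.12 | 6% |
| T1–T5 only, r = 0.5 | 0.500 | 0.33 | 18% |

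The T1–T5 rows use weights 0, 0.125, 0.25, 0.25, 0.25 and 0.125, so b = r and V = 0.3 × 0.219 + 0.7 = 0.766.

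**Step 5: carry-over of imbalance.** Each 0.01 difference in mean baseline utility shifts the T0–T5 QALY difference by 0.01 × b, which is 0.004 to 0.007. With SD 0.20 and 88 per arm, the standard error of the baseline difference is 0.20 × √(2/88) = 0.030. At r = 0.5, an imbalance of that size moves the QALY difference by 0.615 × 0.030 = 0.019. The unadjusted standard error is √0.974 × 0.030 = 0.030, so the shift is about 0.6 of it.

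**Step 6: check of validity.** This used 4,000 simulated trials at each of three correlations, with no treatment effect, 88 per arm and one common correlation (0.3, 0.5 or 0.7) among all six visits. The *t* test rejected in 5.2%, 4.9% and 5.0% of all trials. Among trials whose baseline imbalance exceeded one standard error, it rejected in 10%, 13% and 14%. The adjusted estimate showed essentially no dependence on the imbalance.

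**The case against.** The strongest reply is that randomisation already makes the comparison valid. That is right. The unadjusted difference is unbiased, the overall type I error is about 5%, and the interval already allows for chance imbalance. A reader might infer that the QALY result is biased, that any baseline difference is counted in full as intervention effect, or that nothing guards against imbalance because no stratification by utility is stated. The documents support none of these. Randomisation guards on average, the carry-over is partial (slope 0.4 to 0.7), and lack of stratification on utility is not a defect.

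A second reply is that T0 may not belong to the QALY at all. The section speaks of a one-year horizon, whereas T0–T5 spans 60 weeks; if the year is T1–T5, the direct weight of T0 is zero. This weakens the point but does not remove it, because most of the carry-over runs through correlation.

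A third reply is that the size rests on assumptions. It does, which is why a range is given and no monetary value is attached.

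A fourth is that an article leaves economic modelling to a fuller plan. That would answer silence, but here a specific unadjusted test is named.

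It is also tempting to make the same claim for costs. Pre-randomisation cost is not part of the cost total. Table 2 is not shown, so collection of the TiC-P at T0 cannot be confirmed, although healthcare appointments are listed among the baseline variables. The Discussion's remark on controlling for appointments might reach costs, but it names no outcome.

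**Conclusion.** The point holds as one of efficiency and of sensitivity to the realised baseline imbalance, not as an error that invalidates the analysis. On the T0–T5 reading, adjusting for baseline utility would cut the standard error of the QALY difference by about 9% to 31%, with 22% at a correlation of 0.5. On the T1–T5 reading the cut is 18% at 0.5 and 6% at 0.3. These figures rest on the assumed correlations; the absolute shift of 0.019 QALY rests also on the assumed SD of 0.20.

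Only the economic evaluation is affected; the EDE-Q primary test is not. The QALY part stands on the text alone, because the article confirms EQ-5D-5L at baseline. For costs the gain is secondary and conditional on baseline collection: at an assumed correlation of 0.3, 0.5 or 0.7 between baseline and follow-up cost, √(1 − r²) gives standard-error ratios of 0.95, 0.87 and 0.71.

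**What to change.** Replace the *t* test on QALYs by a regression of QALY on condition plus T0 EQ-5D-5L utility. Fit the same regression within each of the 1000 bootstrap samples, so that the confidence intervals and acceptability curves are baseline-adjusted too. State whether the one-year QALY runs from T0 or from T1; the adjustment applies either way.

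If the ICECAP-A and TiC-P are collected at T0, treat the capability outcome (with T0 ICECAP-A) and costs (with baseline TiC-P cost) in the same way. The unadjusted comparison can be kept as a sensitivity analysis.

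The cost is about two sentences of analysis text and a few lines of code. For QALYs it needs no new data, and it needs no extra participants.
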